## Abstract

**Background:**

People with substance use disorders generally have unhealthy diets, including limited intake of fruit and vegetables. Evidence shows substantial health benefits from increasing fruit and vegetable consumption on various indicators and possibly also psychological distress. A pilot study has indicated that supplementation with fruit smoothie could be promising also among people receiving opioid agonist therapy for opioid dependence. *FruktBAR* will compare the efficacy of added fruit smoothie supplementation to people receiving opioid agonist therapy compared to standard treatment without added supplementation.

**Methods:**

*FruktBAR* is a multicentre, randomised controlled trial. The trial will aim to recruit 302 patients receiving opioid agonist therapy. The intervention involves daily supplementation with 250 ml fruit smoothie including a variety of fruits such as apple, pineapple, mango, bananas, orange, blueberries, passion fruit, coconut, lime, and blackcurrant. The main endpoints are 16 weeks after intervention initiation. Participants will be included and followed up during and after the intervention. The target group will be patients with opioid dependence receiving opioid agonist therapy from involved outpatient clinics in Bergen and Stavanger, two of the largest cities in Norway. The main outcome is psychological distress assessed with Hopkins Symptom Checklist (SCL-10) at the end of the intervention period 16 weeks after initiation, and will be compared between the intervention and control arms. Secondary outcome measures are changes in fatigue, physical functioning assessed with a 4-minute step-test, health-related quality of life, biochemical indicators of inflammation, and biochemical indicators of fruit intake.

**Discussion:**

This study will inform on the relative advantages or disadvantages of fruit supplementation in addition to the current medically and psychologically oriented treatment of people receiving opioid agonist therapy. If the supplementation is efficacious, it can be considered for further scale-up.

**Trial registration:**

Registered 2022-02-08 in ClinicalTrials.gov, identifier NCT05229770.

## Background

People with substance use disorders and particularly those with opioid dependence, have high morbidity, reduced quality of life, and a high risk of early mortality [1, 2]. Studies on people with opioid dependence in comparable settings have shown diet patterns with a low intake of fruits and vegetables, reflected in biochemical indicators [3, 4]. Folic acid and carotenoids are among the biochemical markers of intake of fruits and vegetables, and studies show correlations between these biochemical markers and longevity [5]. An inadequate intake of vegetables and fruits could be a risk factor for diseases and early deaths, and an increase in these could have beneficial effects on several health outcomes [5–7]. High consumption of fruits and vegetables is associated with a reduction in cardiovascular disease, cancers, and all-cause mortality.

In the Oslo Antioxidant study, a randomized controlled trial, people smoking tobacco received either kiwi fruits, a combination of various antioxidant-rich foods including fruit smoothies, or none except their habitual regular diet [8]. This study observed changed gene expressions linked with cellular protective mechanisms after an eight-week intervention period with kiwi or antioxidant-rich foods. Another randomized controlled trial among people with chronic obstructive lung disease in Greece showed less progression of lung diseases among those increasing the consumption of fruits and vegetables substantially [9]. Trials have also shown promising findings on psychological distress of healthy diets, including increasing fruits and vegetables in addition to other elements [10, 11]. The impact of fruit smoothie supplementation alone is uncertain, as its potential impact on inflammation [12].

Very few experimental studies focusing on nutrition have been conducted among people with substance use disorders. To our knowledge, there are no other trials having investigated the effects of fruits and vegetables on people with substance use disorders aiming to improve mental health and physical functioning. A recently conducted pilot study by our team with a similar intervention has shown favourable experiences [not yet published]. Thus, we will conduct a multicentre randomised controlled trial to test if daily intake of fruit smoothie over sixteen weeks could improve psychological well-being, physical function tests, and biochemical indicators.

## Objectives

This paper presents the protocol of the FruktBAR. The primary objective is to compare the effect of a daily supplement of 250 ml fruit smoothie on the level of psychological distress among people with substance use disorders receiving the OAT from outpatient clinics in Bergen and Stavanger (intervention arm), compared with standard treatment without supplement.

Secondary objectives are comparing the trial arms regarding physical function tests, fatigue, assessment of changes in quality of life, and biochemical indicators, including inflammation.

## Methods

### Study design

The study design of this study is a multicentre individually randomised controlled trial.

### Study settings and participants

The target group will be patients with opioid dependence receiving OAT from involved outpatient clinics in Bergen and Stavanger. Bergen and Stavanger have adopted an integrated treatment and care model for patients receiving OAT. In Bergen, OAT outpatient clinics are located in each district with follow-up of patients by health and social workers on a weekly basis with observed intakes of the OAT medications [2]. The OAT outpatient clinics are staffed by a consultant and a junior physician, in addition to nurses, psychologists, and social workers. This treatment model for people receiving OAT treatment provides a well-suited platform to test the integration of further interventions aiming to improve their health and life span.

### Eligibility criteria

Inclusion criteria for the trial areReceiving weekly OAT outpatient follow-up from an included outpatient clinicHaving fruit and vegetable intake below five portions per day (assessed at screening)Giving informed consent

The following exclusion criteria will be used:Allergies or prior anaphylactic reactions involving fruits or vegetablesPoorly regulated diabetes type 1 or 2 (HbA1c ≥54 mmol/mol)

### Interventions

Participants randomised to the intervention arm will receive a 250 ml fruit smoothie as a diet supplement for sixteen weeks. The fruit smoothies will be marketed products including combinations of the following fruits: apple, pineapple, mango, bananas, orange, blueberries, passion fruit, coconut, lime, and blackcurrant. The participants will receive a mixture of different smoothie types with the option of removing alternatives based on preferences. Fruit smoothie products will come in plastic bottles and will be delivered directly to the participants. Each participant will receive seven smoothie bottles per week with an oral agreement with each participant to consume one of these per day. Delivery of fruit smoothie will generally be given in parallel with the delivery of OAT medication. Participants randomised to standard treatment will receive regular OAT clinic follow-up without added supplementation.

### Outcomes

The primary outcome is psychological distress assessed with the Norwegian validated translation of the ten-item version of the Hopkins Symptom Checklist (SCL-10) in the mid of the intervention period 16 weeks after initiation (12–16) [13]. This will be evaluated with the mean SCL-10 item score and compared between the intervention and control arms.

Secondary outcomes are also measured at the same time 16 weeks after initiation and include the following:

Changes in fatigue assessed with the Fatigue Symptom Scale (FSS-3) [14]Physical functioning assessed with a 4-minute step-test that measures the number of steps climbed in 4 minutes [15]Changes in health-related quality of life assessed with the five dimensions and five level EuroQoL scale (EQ-5D-5L), as well as a self-reported question on happiness with a 0 to 10 visual analogue scale [16]Change in biochemical indicators of inflammation (compared to baseline estimates)All participants: Mean concentration of C-reactive protein in serum and total leukocyte count in bloodRandomized sub-group (*n* = 60, 1:1 intervention:control arm): IFN-gamma, IL-1beta, IL-1RA, IL-6, IL-8, IL-10, IL-17A, MCP-1, TNF-alfa measured in dried blood spotsBiochemical indicators of fruit intake (compared to baseline estimates)All participants: Folic acid levelsRandomized sub-group (*n* = 60, 1:1 intervention:control arm): carotenoids (vitamin A-related compounds) measured in dried blood spots

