### Sample size

We calculated sample sizes for a two-sample means test based on the following assumptions:The power is set at 90% with a two-sided alpha (α) error of 5%.Mean SCL-10 score in the control arm is 2.2 (SD: 0.8). This is based on data from a similar cohort [17].Mean SCL-10 score in the intervention arm is 1.90 (SD: 0.8).Intervention:control ratio of 1:1.

Based on the above-mentioned assumptions, 302 persons are required (151 in the intervention arm and 151 persons in the control arm). Statistical power was calculated in Stata SE 17.0.

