## Discussion

The research project will improve understanding of potential effects of an intervention increasing the daily intake of fruit smoothie over a period of sixteen weeks, and whether it could improve mental health, affect inflammation, and physical functioning. If found effective, this could potentially reduce the large morbidity and mortality among people with substance use disorders receiving OAT. There is a range of known interventions relevant to people with substance use disorders, including OAT and treatment of concurrent infections [22, 23]. If our trial is found effective, dietary interventions could potentially be integrated into a more comprehensive treatment model.

Our trial involves both a few limitations and several strengths. The trial is not fully blinded, although some masking measures are taken, including blinding of analysts, not informing patients on hypothesis, and using different people delivering the intervention and assessing the outcomes. The public funding of the study, ensures independency. The use of biological indicators that could be linked with the primary outcome reduces the risk of information biases. Further, the study is individually randomised, which minimizes potential confounding. The sample size of the study is sufficiently large to answer the primary objectives with a high degree of precision and is also assumed to have adequate precision for secondary objectives. Relating to safety, the trial is considered a low-risk study. Our trial design is less vulnerable to confounding from time trends than designs such as stepped-wedge designs.

If the fruit smoothie supplementation compared to standard care is efficacious in improving treatment outcomes, the intervention could have potential for scale-up.

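### Fatigue, quality of life and the biomarkers are worded as change from, or comparison with, baseline, and no adjustment for the screening value is stated, which risks a less precise between-arm comparison

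*Protocol article*

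**What the plan says.** All references are to the protocol article.

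- **Outcomes, primary:** SCL-10 is a mean item score at the week-16 assessment, compared between the arms.
- **Outcomes, secondary:** fatigue appears as "Changes in fatigue assessed with the Fatigue Symptom Scale (FSS-3"). Health-related quality of life (EQ-5D-5L) is also worded as change. The inflammation item reads "Change in biochemical indicators of inflammation (compared to baseline estimates"). The fruit-intake item carries the same parenthesis without the word change. The step-test is not worded as change.
- **Biomarker subgroup:** 60 participants, drawn 1:1 from the two arms.
- **Objectives:** "Secondary objectives are comparing the trial arms regarding physical function tests, fatigue", and the sentence goes on to quality of life and the biochemical indicators.
- **Analyses and statistical methods:** linear mixed models are named for the main outcomes, without saying how baseline enters. The one adjustment stated is for substantially imbalanced potential confounders, in sensitivity analyses. A detailed analysis plan is to follow before data export.
- **Discussion:** the sample size "is also assumed to have adequate precision for secondary objectives".
- **Table 1:** FSS-3, EQ-5D-5L, the step-test and biochemical tests are scheduled at screening and at week 16.

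**The concern.** The secondary outcomes do not share one form. The step-test is a plain measurement, fatigue and quality of life are changes, and the biomarkers have baseline as the only comparator named beside them. An analyst who takes these definitions as they stand would subtract the screening value and compare mean change between arms. A mixed model with separate baseline means and an arm-by-time contrast does the same thing.

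Under randomisation that comparison is unbiased, but it fixes the slope on baseline at 1 instead of estimating it, and so loses information the trial already collects. The loss matters most in the subgroup of 30 per arm, where precision is scarce. It also bears on the Discussion's assumption of adequate precision for the secondary objectives. Leaving the form open further allows the choice between change and adjusted value to be made late.

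**Working it through.** **1. The plan's own figure.** The inputs are in Sample size: "The power is set at 90% with a two-sided alpha (α) error of 5"%; "Mean SCL-10 score in the control arm is 2.2 (SD: 0.8"); "Mean SCL-10 score in the intervention arm is 1.90 (SD: 0.8"); "Intervention:control ratio of 1:1". The difference is 2.2 − 1.90 = 0.30, or 0.30/0.80 = 0.375 SD. The normal approximation gives 150 per arm. The t-based solution is 150.41, rounded up to 151 per arm, or 302 in total. The stated figure reproduces exactly. It concerns SCL-10 only.

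**2. Variance of three between-arm comparisons.** Let the SD be σ at both times and the baseline to week-16 correlation be rho. Per participant:

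- unadjusted week-16 value: σ²
- raw change: 2σ²(1 − rho)
- week-16 value adjusted for baseline: σ²(1 − rho²)

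The ratio of raw change to adjusted value is 2(1 − rho)/(1 − rho²) = 2/(1 + rho), which exceeds 1 for every rho below 1. The ratio of raw change to unadjusted value is 2(1 − rho), which exceeds 1 only when rho is below 0.5.

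The document gives no rho, so a range is shown (σ² = 1):

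| rho | raw change | adjusted | change / adjusted |
|---|---|---|---|
| 0.2 | 1.60 | 0.96 | 1.67 |
| 0.3 | 1.40 | 0.91 | 1.54 |
| 0.4 | 1.20 | 0.84 | 1.43 |
| 0.5 | 1.00 | 0.75 | 1.33 |
| 0.6 | 0.80 | 0.64 | 1.25 |
| 0.7 | 0.60 | 0.51 | 1.18 |
| 0.8 | 0.40 | 0.36 | 1.11 |

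**3. Illustration with all participants.** The document gives no effect size for these outcomes, so the SCL-10 value of 0.375 SD is borrowed purely as a yardstick. With 151 per arm, full data and two-sided 5%, power = Φ(0.375/(s·√(2/151)) − 1.96), where s is the square root of the variance above.

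| rho | unadjusted week 16 | raw change | adjusted |
|---|---|---|---|
| 0.3 | 90.3% | 78.6% | 92.7% |
| 0.5 | 90.3% | 90.3% | 96.4% |
| 0.7 | 90.3% | 98.8% | 99.5% |

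**4. Subgroup of 30 per arm.** The difference detectable with 80% power is (1.960 + 0.842)·s·√(2/30), in SD units. This step needs no borrowed effect size.

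| rho | unadjusted week 16 | raw change | adjusted |
|---|---|---|---|
| 0.3 | 0.72 | 0.86 | 0.69 |
| 0.5 | 0.72 | 0.72 | 0.63 |
| 0.7 | 0.72 | 0.56 | 0.52 |

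**The case against.** The strongest reply is that an outcome metric is not an analysis model. If baseline is a covariate, modelling change or modelling the week-16 value gives the same treatment estimate: Y₁ − Y₀ = a + bT + cY₀ is the same model as Y₁ = a + bT + (c + 1)Y₀, with the same b and the same standard error. A mixed model with a common baseline mean recovers the same efficiency, and how baseline enters a model is ordinary analysis-plan content. The algebra is right, and the protocol does not commit to an unadjusted subtraction. But nothing shown commits to the covariate either. The outcome wording points towards subtraction, and the only adjustment stated is confined to imbalanced confounders in sensitivity analyses. What stands is therefore a definition to tighten, not an error in a fixed model.

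Two stronger readings are tempting, and the document supports neither.

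- **A before-after analysis.** A reader might infer from the parenthesis on baseline that the biomarkers are tested within arm, giving up the randomised comparison. The Objectives say the arms are compared on the biochemical indicators, and the subgroup is drawn equally from both arms. A change can be compared between arms, and that is the plain intent.
- **Change is always noisier than the week-16 value.** This needs rho below 0.5. At 0.5 the two are equal, and above it change is the more precise.

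It is also fair to object that 0.375 SD belongs to SCL-10. The power figures illustrate the loss; they do not refute the Discussion's statement on precision.

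**Conclusion.** The point holds as a modest one about secondary outcomes. As worded, fatigue, quality of life and the biomarkers invite a between-arm comparison of raw change, or a mixed model without a common baseline mean. Compared with adjustment for the screening value, this inflates the variance by 54% at rho 0.3, 33% at 0.5 and 18% at 0.7. If rho is below 0.5, it also does worse than ignoring baseline.

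These figures assume equal SDs at both times, and rho is assumed throughout. The power and detectable-difference figures further assume full data and approximate normality, so they are only indicative for markers that are often skewed, such as CRP and the cytokines. The loss does not arise if the unseen analysis plan already includes each outcome's baseline as a covariate or constrains the baseline means to be equal. Neither the SCL-10 analysis nor the 302 participants is called into question.

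**What to change.** In Outcomes, for every secondary outcome with a screening value, state the estimate as the between-arm difference at week 16, adjusted for that participant's own screening value of the measure. A linear mixed model with a common baseline mean is an equivalent choice. Replace the parenthesis on baseline estimates, in both biomarker items, with *compared between arms, adjusted for baseline*. Name a suitable scale for skewed markers such as CRP and the cytokines. Carry the same specification into the detailed analysis plan, and make clear that this adjustment belongs to the main analysis of these outcomes and does not depend on observed imbalance.

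The cost is wording only. Table 1 already schedules FSS-3, EQ-5D-5L, the step-test and biochemical tests at screening. The happiness item has no line of its own there, so confirm that it is recorded at screening before adjusting for it. No additional participants or visits are needed.

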### Sample size

We calculated sample sizes for a two-sample means test based on the following assumptions:The power is set at 90% with a two-sided alpha (α) error of 5%.Mean SCL-10 score in the control arm is 2.2 (SD: 0.8). This is based on data from a similar cohort [17].Mean SCL-10 score in the intervention arm is 1.90 (SD: 0.8).Intervention:control ratio of 1:1.

Based on the above-mentioned assumptions, 302 persons are required (151 in the intervention arm and 151 persons in the control arm). Statistical power was calculated in Stata SE 17.0.

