### Recruitment

All patients receiving OAT treatment from included clinics will be considered the reference target population. As part of an annual clinical assessment of patients receiving OAT linked to the ATLAS4LAR project [18], patients will receive information about the study and will be asked for consent to participate. All patients in the target population with inclusion and no exclusion criteria will be offered study participation until the targeted sample size has been reached. Participants giving informed consent will receive an extended clinical assessment, and be randomised for the study.

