### Analyses and statistical methods

A detailed analysis plan will be developed before data export and data analysis. Analysis methods will be conducted in line with the CONSORT and SPIRIT guidelines as far as possible [19–21]. Two-sided tests will be used, and *p* < 0.05 will be used as the statistical significance threshold. Descriptive tables for the participants will be presented with categorical variables that will be summarized with percentages, and for continuous variables as medians with interquartile ranges, or means with standard deviation for continuous variables with a Gaussian distribution. The main outcomes will be analysed with linear mixed models. Efficacy estimates of the outcomes will be presented with 95% confidence intervals. If there are substantial imbalances in potential confounders at baseline, estimates with adjustments for these will be presented in sensitivity analyses. For missing data, appropriate imputations based on pre-defined assumptions and analysis plan will be done when necessary.

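### The 302 needed with week-16 SCL-10 data is also the number recruited, so the stated 90% power makes no allowance for loss

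*Protocol article*

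**What the plan says.** The sample size section of the protocol article describes a two-sample means test with 90% power, two-sided 5% alpha, mean SCL-10 of 2.2 in the control arm and 1.90 in the intervention arm, SD 0.8 in both, and 1:1 allocation. From these it concludes that "302 persons are required (151 in the intervention arm and 151 persons in the control arm". Loss to follow-up is not among the listed assumptions.

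The same number governs enrolment. The abstract says "The trial will aim to recruit 302 patients receiving opioid agonist therapy", and under Recruitment eligible patients "will be offered study participation until the targeted sample size has been reached". Those who consent are then randomised.

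The section on analyses and statistical methods names linear mixed models for the main outcomes and adds: "For missing data, appropriate imputations based on pre-defined assumptions and analysis plan will be done when necessary". It gives no expected rate. Table 1 schedules SCL-10 at screening, at week 16 (window 12–16) and after the intervention. The Discussion states: "The sample size of the study is sufficiently large to answer the primary objectives with a high degree of precision".

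**The concern.** A sample size from a two-sample test is the number of outcomes in the analysis. Here the primary outcome is SCL-10 at week 16, so the 302 are people with that measurement. Once 302 is also the point at which recruitment stops, the 90% holds only if follow-up is essentially complete. The protocol does not claim that it will be, and it provides for imputation.

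This is not a detail that can wait for the analysis plan. That plan can choose the model and the handling of missing data, but it cannot add participants once recruitment has closed at 302. What is at stake is how a null result is read. Readers will set it against a 90% figure that applies to a complete data set, and the Discussion relies on the same number.

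**Working it through.** **Inputs (Sample size section).** Difference 2.2 − 1.90 = 0.30; SD 0.8; two-sided alpha 0.05; power 0.90; ratio 1:1.

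**Step 1: reproduce 302.** Normal approximation: n per arm = 2 × (1.960 + 1.282)² × (0.8/0.30)² = 149.4, so 150. With the t distribution, power comes from the noncentral t with 2n − 2 degrees of freedom and noncentrality 0.30 / (0.8 × √(2/n)):

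- n = 151 per arm: noncentrality 3.258, power 90.1%
- n = 150 per arm: noncentrality 3.248, power 89.9%

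The smallest n per arm reaching 90% is therefore 151, or 302 in total. The protocol's figure reproduces exactly, with no margin for loss inside it. A single missing outcome (151 against 150) leaves 90.0%; one missing in each arm takes power below 90%.

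**Step 2: power if 302 are randomised and some are lost.** The protocol gives no loss rate, so a range is assumed. The number analysed per arm is 151 × (1 − loss), rounded, with the same test and inputs.

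| Assumed loss | Analysed per arm | Power, unadjusted test |
|---|---|---|
| 0% | 151 | 90.1% |
| 5% | 143 | 88.5% |
| 10% | 136 | 86.9% |
| 15% | 128 | 84.8% |
| 20% | 121 | 82.8% |
| 25% | 113 | 80.1% |
| 30% | 106 | 77.6% |

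**Step 3: what baseline adjustment could recover.** If the model uses screening SCL-10 with correlation r to the week-16 score, the residual SD is 0.8 × √(1 − r²): 0.763 at r = 0.3, 0.733 at r = 0.4 and 0.693 at r = 0.5. Putting this into the same power formula, and treating participants without a week-16 score as contributing nothing:

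| Assumed loss | r = 0.3 | r = 0.4 | r = 0.5 |
|---|---|---|---|
| 10% | 89.8% | 91.9% | 94.5% |
| 20% | 86.1% | 88.7% | 91.8% |
| 30% | 81.3% | 84.3% | 88.1% |

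Adjustment offsets the loss when 1 − r² equals 1 − loss, that is, when r = √loss: about 0.32 at 10% loss and 0.45 at 20%. The protocol states no correlation, so r is also an assumption.

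**Step 4: the alternative of enrolling more.** Keeping 302 with week-16 data would require 2 × 151/(1 − loss), rounded up per arm: 336 at 10% loss and 378 at 20%.

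**The case against.** The calculation is right, so this is not an arithmetic error, and the shortfall exists only if outcomes are missing. Both points stand. At 5% loss the drop from 90.1% is under two percentage points.

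The setting may also favour retention. Eligibility requires weekly outpatient follow-up, smoothies are generally delivered together with the opioid agonist medication, and the assessment window spans weeks 12 to 16. The high mortality described in the Background is not a 16-week attrition rate. This is fair, and it means that no particular loss can be read out of the protocol. It does not show that loss will be nil.

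The strongest reply is that the primary analysis is a linear mixed model, not the unadjusted test, and that SCL-10 is measured at screening. Such a model, or imputation drawing on the screening and post-intervention scores, can recover part of what is lost, and baseline adjustment could bring power to 90% or more. This stands as a possibility. However, the protocol does not say how baseline enters the model, and its calculation takes no credit for it.

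A reader might go further and infer that the trial is underpowered, or that its type II error is about twice the stated 10%. The protocol does not support either reading. The doubling needs roughly 20–25% loss and no gain from baseline, and neither is stated. Nor does an expected 95% confidence interval half-width of about 0.18 against an effect of 0.30 reveal a defect. A ratio near 0.6 (1.960/3.242) follows from any design with 90% power at two-sided 5%.

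**Conclusion.** The point holds in a limited form. The 302 is the uninflated number of participants with week-16 SCL-10, and it is also used as the number recruited and randomised. On the protocol's own unadjusted test, the stated 90% therefore requires essentially complete outcome data. With loss it falls to about 88.5% at 5%, 86.9% at 10%, 82.8% at 20% and 77.6% at 30%.

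These figures take the protocol's means and SD as given, assume equal loss in the two arms, and use assumed loss rates. Power under the planned mixed model may lie above or below 90%, depending on the actual loss, on whether baseline SCL-10 is in the model, and on its correlation with the outcome. The protocol settles none of these. It is a weakness in how sample size and power are stated. It should be corrected, but it does not invalidate the design.

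**What to change.** Keep 302 randomised and restate what the number delivers. Suggested wording: *302 participants with week-16 SCL-10 give 90% power on an unadjusted two-sample test. We expect x% to have no week-16 score. With 302 randomised, power is then y% on the unadjusted test and z% under the planned linear mixed model with baseline SCL-10 as a covariate, assuming a baseline to week-16 correlation of r.* At 20% loss, for example, y is 82.8, and z is 91.8 if r = 0.5 or 86.1 if r = 0.3. The values of x and r should come from the sponsor's own pilot or cohort data where available. The model specification should then name baseline SCL-10 as a covariate, so that the claimed gain is actually realised.

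The cost is a change of wording and a slightly less favourable unadjusted power. No new measurement is needed, because SCL-10 is already collected at screening. If the sponsor would rather keep 90% on the unadjusted test, the recruitment target would have to rise as in step 4 of the working, which is a much larger change.
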